### Planned analysis

Since this study primarily seeks to determine the feasibility and user-perceived acceptability of the intervention, the analysis will focus on key parameters required to conduct a future larger trial. Majority of the analysis will be reported descriptively. The study will measure feasibility of the recruitment, enrolment process, treatment delivery, and data collection. The study screening log, enrolment log, attendance list and study records will be used to descriptively inform these outcomes. User-perceived acceptability of engaging and satisfaction of the intervention will be measured and reported descriptively using journal entries, treatment feedback questionnaire, and feedback semi-structured interviews. Journal entries, treatment feedback questionnaires, and feedback semi-structured interviews will also be analyzed qualitatively using thematic analysis. Thematic analysis will be conducted first manually utilizing Braun and Clarke’s (2019) [48] six-step process and with NVIVO 10 software [49]. Two researchers will validate the analysis, and any disagreements will be resolved using a third researcher. Using thematic analysis will facilitate an essentialist method that enables reporting of meanings, experiences, and the participant’s reality, which fits well with the aims and objectives of this study (determining feasibility and acceptability) [48, 49]. The process of thematic analysis will also enable the reporting of secondary outcome measures on the impact of the intervention (i.e., benefits of the intervention, changes in participant’s viewpoints, and feeling of burnout).

Secondary outcome measures using questionnaires will be analyzed following the Intention to Treat (ITT). ANOVA or chi-square will be used to compare the sociodemographic data and baseline outcome measures (T0) [50]. Secondly, longitudinal changes (baseline, post-treatment, and 1 month and 3 months follow-up) and the differences between the two groups will be examined using mixed linear models as these models are more precise than the repeated measures of ANOVA [50]. Missing or incomplete data will be considered in the ITT analysis using maximum likelihood estimation method [50]. Effect sizes will be calculated using Cohen’s *d* (bias corrected) to represent the difference between Standard Mean Changes (MC) (T0-T2, T0-T3, T0-T4) [50]. Calculation of SMC in each group will be conducted, providing the *d* index of the general effect size from the differences between combined Individualized Management Plan (IMP) and Professional Problem-Solving Peer (PPSP) debrief vs. informal peer debrief [50]. After the data is analyzed, summary tables will be provided for all planned evaluations at pre-treatment (T0), post-treatment (T2), 1 month follow-up (T3), and 3 months follow-up (T4) [50]. Results will be reported as frequencies and descriptive statistics (mean, standard deviation, and percentages), summarizing the characteristics of the total sample and participants within each group [50].

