This study will administer a professional peer debrief led by accredited peer support leader(s). It will include a semi-structured, 6-week, group-based, virtual, informal, peer debrief session. The peer debrief session aim to encourage social interactions and engagement between participants rather than to achieve structured debrief objectives, such as successful reflection. The objectives are weighted towards achieving peer support using informal structures of debrief. The peer debrief will also incorporate the theory of social problem-solving. The goal for peer debrief is to learn and apply problem-solving approaches [38]. The peer support leader will support participants to positively change problematic situations and/or provide techniques to decrease emotional distress from the afflicted problem [38]. This will be facilitated through group discussions, experience sharing, and individual guidance to summarize the causes of the problem, develop feasible goals and strategies, and perform analysis on the effects (success or failure) of the implemented strategy [38].

The purpose of integrating IMP was due to the key component of ‘tailoring’, which was identified in Adnan et al. (2022) refined program theory [32, 33]. Tailoring caters towards the individual’s experience, addressing contextual factors and mechanisms. It also facilitates understanding of the unique characteristics and experiences of the individual, which may allow investigators to address their individual’s needs, resources, preferences, and goals; ultimately giving meaning to the intervention, increasing personal relevance, and prioritizing the user’s control and involvement. Moreover, debrief facilitates the reflection of situations, exploring one’s thoughts, and questioning assumptions to achieve positive learning that is based on lived experiences [39]. An individual’s performance can also be revisited to enable greater understanding of the situation, foster critical thinking, and provide adjustments toward future situations [39].

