#### Active control group

The informal peer debrief will include mutual support between participants with shared experiences. Like PPSP debrief, its goals are not to achieve debrief outcomes, rather, to encourage social interaction and engagement between participants—enabling a platform to discuss concerns, problems, and feelings [40]. The informal peer debrief will be a semi-structured, 6-week, group-based virtual, peer debrief intervention. Peer support leader(s) will conduct the sessions but will not provide active solutions. The list of semi-structured questions will be consistent in both intervention and control debrief groups with differences in the ‘Pre-briefing’, ‘Discovering’, and ‘Deepening’ sections; informal peer debrief will not include problem-solving approach (see Table 2).

**Table 2 pone.0285038.t002:** Debrief session layout.

Topic	Content
Introduction	• Introduction of the support leader and researcher present in the session • What this study is about and who is conducting the study
**Pre-briefing**	• Purpose of the debrief session and the role of the support leader in facilitating discussions and prompting self-reflection • Items that can be discussed (i.e., encounters/stressors at the workplace) • **Management of situations using problem-solving approaches and connecting new learnings into future situations.**
Defusing	• Encouraging participants to talk about how they feel when encountered with a stressful situation. • Allow reflection of their feelings and recapping the scenario
**Discovering**	• Allow other participants to reflect on the situation and provide their thoughts and ideas • Enable participants to explore any similar situations that they may have encountered. • **Support leader(s) may ask other participants on how they would approach the situation, their rationale, and potential future strategies. The support leader(s) can also offer their own mental model on problem-solving approaches to deal with the situation.**
**Deepening**	• **Reflection on what can be done in similar future situations.** • **Finding a relationship between the suggested strategy to other situations at work.**
Summary	• Recapping what was discussed in the session • Ending with one thing that can be taken away from the session and used in their workplace.

Note: The intervention group (PPSP debrief) will also use techniques stated in both ‘roman’ and ‘bold’ typeface, whereas the control group will follow techniques noted in ‘roman’ typeface only.

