### Sample size estimation

To achieve the primary aims of determining feasibility and acceptability, a pragmatic approach will be taken in that if sufficient data to address the secondary aim (preliminary effectiveness) can be achieved, this should also be sufficient for the primary aim. Power calculations were therefore conducted to determine the sample size required for the secondary aim of this study.. Analyses variance with repeated measures between and within the design in relation to the participants wellbeing was used, with low effect size estimated (η^2^ = 0.061). Significance level was 0.05 and power at 0.95. This resulted to a minimum sample of 106 participants for the study, having considered 20% attrition rate. The sample size was rounded off to 110 participants (55 each group) to enable equal samples sizes in both groups.

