### Data collection methods

Baseline (questionnaire scale, sociodemographic, work-related information), journal entry, post-treatment feedback, post-intervention (questionnaire scales), and one- and three-months follow-up (questionnaire scales) assessments will be performed by sending a survey link to participant’s email. Participants will be able to complete the questionnaires on an electronic device, such as a computer, tablet, or smartphone. The questionnaires will be checked weekly after each delivery to ensure participant’s completion. Participants that do not complete the questionnaires within a specified time will be sent a reminder via email. Likewise, if participants do not attend their Individual Management Plan and/or debrief sessions, the research team will contact participants via email to join the session or to re-book into another session during the week. The feedback semi-structured interviews will be conducted by inviting participants to attend a virtual one-on-one semi-structured interview, which will be organized through email communication.

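### Both arms are treated in debrief groups, but the sample size assumes independent participants and the described model names no debrief-group term, so the 95% power and the standard errors hold only if within-group correlation is negligible

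*Protocol article*

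**What the plan says.** All references are to the protocol article.

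- **Unit of randomisation.** Under Study design, individual eligible participants are randomised 1:1.
- **Delivery, intervention arm.** After a one-to-one consult, participants join a debrief run by accredited peer support leader(s): "It will include a semi-structured, 6-week, group-based, virtual, informal, peer debrief session" (Intervention group).
- **Delivery, control arm.** "The informal peer debrief will be a semi-structured, 6-week, group-based virtual, peer debrief intervention" (Active control group). Peer support leader(s) run these sessions too. In both arms the stated aim is interaction between participants.
- **Sample size.** The method is given as follows: "Analyses variance with repeated measures between and within the design in relation to the participants wellbeing was used". The assumed effect is η² = 0.061, at an alpha of 0.05 and a power of 0.95. The outcome of the calculation is then stated: "This resulted to a minimum sample of 106 participants for the study, having considered 20% attrition rate". After that the total becomes 110, or 55 per arm. No design effect, ICC or debrief group size appears.
- **Analysis.** Under Planned analysis, longitudinal change and the between-arm difference "will be examined using mixed linear models as these models are more precise than the repeated measures of ANOVA". No debrief-group effect is named.
- **Attendance.** Those who miss a session may be invited "to re-book into another session during the week" (Data collection methods). The Measurements section plans an audit of attendance at consults and debriefs in both arms, but does not say that the list identifies the debrief group.

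**The concern.** This is an individually randomised group-treatment design. People in one debrief group share discussions, peers and a leader for 6 weeks, and the interaction is meant to be what works. Their post-baseline outcomes can therefore be expected to correlate, in both arms. A sample size that counts each person as independent then overstates information. A model that handles repeated measures within a person, but not people within a group, gives standard errors that are too small.

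Two things are at stake. First, the trial is sized on the secondary effectiveness aim, and the Discussion expects statistically significant benefit and presents the sample size as a strength. A false-positive rate above 5% could wrongly support the larger trial. Second, Planned analysis says the work will focus on parameters needed for that larger trial. For a group-delivered intervention the ICC is one of them, and nothing plans to estimate it.

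**Working it through.** **The plan's own figure.** Inputs from Sample size estimation: η² = 0.061, so f² = 0.061/0.939 = 0.065 and f = 0.255; alpha 0.05; power 0.95; 20% attrition. The tested effect, the correlation between measurements and any sphericity correction are not stated. The questionnaires have four time points (Measurements).

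- Group-by-time interaction, correlation 0.5: 36 completers, or 36/0.8 = 45 recruited.
- Between-arm effect, correlation 0.5: 128 completers, or 128/0.8 = 160 recruited.
- Interaction with η² read as partial (noncentrality = N × 3 × f²): 90 completers. 90 × 1.2 = 108, close to 106; 90/0.8 = 112.5 is not. Power at 88 completers is 94.7%.

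So 106 is not uniquely fixed by the stated inputs. None of these variants includes clustering. Below, the stated 95% is taken as given at 110 × 0.8 = 88 completers.

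**Allowing for groups.** Group size and ICC are assumptions: 6, 8 or 10 enrolled per group, so m = 4.8, 6.4 or 8 analysed after 20% attrition, and an ICC of 0.01 to 0.10. For a one-degree-of-freedom contrast:

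- design effect DE = 1 + (m − 1) × ICC
- actual alpha if groups are ignored = 2 × [1 − Φ(1.960/√DE)]
- power = Φ[(1.960 + 1.645)/√DE − 1.960]
- effective number = 88/DE

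| Enrolled per group | m | ICC | DE | Actual alpha | Power | Effective number |
|---|---|---|---|---|---|---|
| 6 | 4.8 | 0.01 | 1.04 | 5.4% | 94% | 85 |
| 6 | 4.8 | 0.02 | 1.08 | 5.9% | 93.5% | 82 |
| 8 | 6.4 | 0.05 | 1.27 | 8.2% | 89% | 69 |
| 10 | 8 | 0.05 | 1.35 | 9.2% | 87% | 65 |
| 10 | 8 | 0.10 | 1.70 | 13.3% | 79% | 52 |

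Worked for the last row: DE = 1 + 7 × 0.10 = 1.70 and √1.70 = 1.304. Alpha = 2 × [1 − Φ(1.503)] = 0.133. Power = Φ(2.765 − 1.960) = Φ(0.805) = 0.79. The model standard error is understated by 1 − 1/1.304 = 23%.

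**Few groups.** With m from 8 down to 4.8, the 88 completers form 88/8 = 11 to 88/4.8 ≈ 18 groups over both arms, leaving about 9 to 16 between-group degrees of freedom. Testing on those degrees of freedom lowers power further. At m = 8 it is 79% rather than 87% for an ICC of 0.05, and 69% rather than 79% for an ICC of 0.10.

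**Dependence on the baseline.** These powers are relative to the stated 95%. Under the interaction variant with correlation 0.5, power at 88 completers stays above 99% even at a design effect of 1.90. Under the between-arm variant it is about 85% before any clustering.

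**The case against.** The strongest reply is that Planned analysis names mixed linear models and fixes no random-effects structure. A debrief-group effect would fit that wording, and such detail is commonly left to a statistical analysis plan, which is not shown. This stands in part. A reader might infer that the analysis will certainly ignore the groups; the text does not establish that. It shows only that the model is described for time and arm and justified by precision over repeated-measures ANOVA. The sample size point does not depend on an unseen plan, because the calculation is reported as complete, with attrition as its only allowance.

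Other objections that stand:

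- The direction needs a positive ICC, and the size rests wholly on assumed group sizes and ICCs. At an ICC of 0.01 the design effect is negligible.
- Applying enrolled group sizes of up to 10 to the completers would give a design effect of 1.90, alpha of 15.5% and power of 74%. That is too severe, since attrition also shrinks the groups.
- The primary outcomes are feasibility and acceptability, reported mainly descriptively. Clustering does not invalidate them.
- A reader might infer from the re-booking sentence that participants could move to the other arm. The text does not say the other session is in the same arm, but nothing suggests crossing, and the arms have distinct session content. What re-booking does imply is that group membership may be partly fluid. That may soften the clustering but does not remove it.
- With about 5 to 9 groups per arm, the pilot's ICC estimate will be imprecise.

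**Conclusion.** The point holds in conditional form and should be fixed. The sample size makes no allowance for group treatment that the protocol itself describes in both arms, and the model as described has no debrief-group term. With a positive within-group correlation, the 95% power is not delivered; if no such term is added, the standard errors for the secondary effectiveness comparison are also too small.

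Under the assumed 6 to 10 enrolled per group and an ICC of 0.02 to 0.10, the design effect is about 1.08 to 1.70, the actual type I error about 6% to 13%, and power about 93.5% to 79%, before any loss from few between-group degrees of freedom. The size cannot be narrowed from the document, and the 95% it starts from is itself not uniquely reproducible. The feasibility and acceptability conclusions are not touched.

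**What to change.** 1. In the attendance list already planned, record each participant's assigned debrief group and the group actually attended each week. This must be set up before sessions start, because it is hard to reconstruct later.
2. Add to the mixed model a random effect for assigned debrief group, nested in arm and acting on post-baseline outcomes, with Kenward-Roger or Satterthwaite degrees of freedom. This term does not itself model fluid membership; the weekly record shows how much of it there was.
3. In Sample size estimation, restate the power over a stated ICC range using 1 + (m − 1) × ICC with the intended group size, or drop the 95% claim.
4. Report the ICC with its interval, which will be wide, as an output for the future trial.

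Enrolment need not change: this is a pilot whose primary outcomes are descriptive. The cost is one recorded item per session and one model term. The downside is wider intervals, few degrees of freedom and a less favourable stated power.

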## Discussion

Critical care healthcare professionals experience high levels of burnout and mental health implications such as depression, anxiety, and post-traumatic stress disorder [51]. This is relative to chronic occupational stressors that they routinely experience, including high workloads and frequent encounters with adversities [51]. High demands and insufficient resources within critical care implicate to loneliness, poor work engagement and increased levels of burnout symptoms [5, 21, 22]. Amongst the different individual interventions (personal resources) developed to address the symptoms of burnout, peer support demonstrates promising evidence as it targets workplace loneliness, emotional exhaustion, and promotes work engagement [20, 26]. The integration of a problem-solving approach aims to enhance the peer support component through cognitive-behavioral processes to support adaptive coping behaviors [29]. The intervention in this study is also supported by evidence from an expert realist opinion paper (under review) interviewing 21 critical care experts on effective individual interventions. The paper suggested interventions should promote knowledge and skill development, be evidence-based, accessible, inclusive, collaborative, tailored, and promote engagement–which are reflected in the intervention of this study. Tailoring is reflected in the Individualized Management Plan (IMP), which aims to cater to the individual experience and specific needs of end users. The mechanism of self-regulation proposed in the expert opinion was also employed in this study through the integration of a problem-solving approach. Despite strong evidence and theory synthesis supporting the use of these interventions, there have yet to be randomized trials testing and confirming its feasibility, acceptability, and efficacy.

This protocol provides information on a randomized control trial that plans to carry out the intervention based on the combination of tailoring the intervention, peer support, and problem-solving approach on critical care healthcare professionals. The lack of evidence on the feasibility and acceptability of such concepts requires a pilot study to gain greater insight into the preparation process. It is expected that the participants assigned to the intervention group will demonstrate feasibility and user-perceived acceptability of the treatment processes, alongside statistically significant better results in improving wellbeing, work engagement, and decreasing burnout components. The outcomes in this study will be used as preliminary data for the larger and more defined randomized control trial.

One strength identified in this protocol is the inclusion of a large sample size, which is a result from the estimation of the sample size calculations. This provides an opportunity to acquire more accurate mean values, provides smaller margin or error, and identify outliers that may be present (in skewing the data) within smaller samples [52]. The use of randomization, controlled, and the use of two follow-up timepoints in the design of this study may also provide understanding of both immediate and early longitudinal patterns and outcomes of treatment changes of the intervention. A limitation of the study includes the use of an active control intervention, rather than the use of a waitlist control design. Active controls have ethical advantages as it allows the provision of care to participants that are seeking help and enables non-intervention evaluation. However, such designs may produce overestimates of the intervention’s effects and that having an active control counteract and minimize such aspects. Despite this, a greater understanding of the feasibility and acceptability of combining IMP and PPSP debrief is essential to foster a larger study that determines its effectiveness in improving wellbeing, work engagement, and decrease burnout symptoms for critical care healthcare professionals.
